### Multimodal and multidisciplinary intervention

At the hospital, a three-step intervention are planned. First, participating geriatricians will perform a standardized geriatric assessment of each patient to rule out underlying diseases that might cause exhaustion or weight loss and hamper participation in the study. Second, a dietician from the study center will evaluate the nutritional status of patients (Mini Nutritional Assessment, weight, Body Mass Index, weight loss) and analyse the dietary intake reported on a three-day survey given to the patients to complete prior to the visit. On the day, the dietician will also perform calorimetric measurements to estimate dietary needs of each patient. A dietary strategy will be planned and agreed with the patients. The dietician will give written advice to each patient about calorie, protein, calcium, omega-3 fatty acid, and vitamin requirements (Fig. 2). Third, the patient will meet a personal trainer, who is specialized in physical exercise in the older age. A physical training program has been developed for the purpose of the study. It is based on existing validated training programs, with sets of exercises dedicated to three specific targets: muscle reinforcement, balance/flexibility, and endurance. It will consist of daily exercises lasting approximately 30 min and performed 5 days a week. These exercises are simple and require no specific equipment. Three sessions are dedicated to muscle reinforcement (lower limbs, upper limbs, and chest), and two to balance/flexibility and endurance. Intensity will increase over time to improve muscle strength, tailored to the abilities of individual patients. This program will be supported by a dedicated personal trainer, who will evaluate the patients: the personal trainer will explain and demonstrate each exercise to the patient (and caregiver), then the patient will practice each exercise in front of the monitor and be given the opportunity to rectify, and once the monitor has checked that the exercises are fully understood, he/she will hand the patient and caregiver a written handbook with illustrated explanations of the exercises for home training. Patients will be asked to report their activity and adherence to the program in the handbook. A monthly telephone follow-up will be set up, by which the monitor will be able to provide some advice and encouragements to the patients.

**Fig. 2 Fig2:**
[figure not shown]
Nutritional intervention. It is a 3-step intervention with as assessment, an establishment of target and actions, and an action planning in collaboration with the patient

By contrast with the control group, patients in the intervention group will visit the GP at 3 months, who will perform an intermediate SPPB assessment in order to adapt the intensity of the intervention. If SPPB improves by one point or more, no change will be planned, if not they consult the same geriatrician and dietician, and will receive again the physical training program from the personal trainer who will demonstrate the exercises and propose individual (home) or group training sessions (hospital) twice a week for 10 weeks.

### Outcomes and measurements (Table 3)

#### Primary outcome

The primary outcome will be the difference in SPPB scores between inclusion and 6-month visits. To allow comparison, the SPPB will be evaluated by the same GP as far as possible. The SPPB measure reflects the performance status in 3 dimensions: balance, gait, strength/endurance are evaluated by examining ability to stand with the feet together in the side-by-side, semi-tandem and tandem positions, time to walk 4 or 6 m, and time to rise from a chair and return to the seated position 5 times [39].

**Table 3 Tab3:** Schedule of outcome assessments

	Baseline	Intervention Group			Control Group	
		M 3	M 6	M 12	M 6	M 12
SPPB score	X	X	X	X	X	X
Walk test distance	X		X	X	X	X
SPPB	X	X	X	X	X	X
Physical activity	X		X	X	X	X
ADL/IADL	X		X	X	X	X
SF 12	X		X	X	X	X
Serious falls assessments	X		X	X	X	X
Hospitalization	X			X		X
Institutionalization				X		X
Weight, BMI	X	X	X	X	X	X
MNA	X					
Social score	X					
Charlson Index	X					
Medication inventory	X					

*PASE* Physical Activity Scale for the Elderly, *SF12* 12-Item Short Form Health Survey, *BMI* Body Mass Index, *MNA* Mini Nutritional Assessment, *CRP* C-Reactive Protein, *GDS* Geriatric Depression Scale, *GP* General Practitioners, *EPICES Evaluation de la précarité et des Inégalités de santé dans les centres de santé* (in French)

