**Method:**

The PRISME-3P study is a national, interventional, multicenter, cluster randomized trial. Patients over 70 years of age will be systematically screened by their general practitioner (GP) on the basis of clinical criteria of mobility limitation. To avoid contamination bias, the unit of randomization will be the GP practice. In the intervention group, patients will consult a geriatrician and a dietician, and will receive a physical training program from a personal trainer who will demonstrate the exercises and provide follow-up coaching. The control group will receive standard care. The primary outcome will be the change in Short Physical Performance Battery (SPPB) scores between inclusion and 6-months follow-up.

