**Fig. 1 Fig1:**
[figure not shown]
Design of the PRISME 3P randomized controlled trial

In both groups, GPs will perform a consultation for inclusion at baseline and two evaluations at 6 and 12 months thereafter. In the intervention group, an initial blood test will be performed (blood cell count, CRP, pre-albuminemia, and albuminemia). Follow-up will include two visits to the allocated study hospital outpatient clinic (within 2 weeks and at 3 months from inclusion) and 3 visits to the GP (at 3, 6, and 12 months from inclusion). All data collected will be notified by the GPS on the case report form (CRF).

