### Participants

All subjects aged over 70 years old will be eligible except patients with functional or locomotor disabilities, a life expectancy less than 6 months, a progressive chronic disease affecting participation in the program, or a MMSE< 20.

For each consecutive patient over 70 years of age without exclusion criteria, GPs will screen patients with medical interview to detect 2 or more inclusion criteria described in Table 1. These criteria are partly derived from the sarc-f screening tool for sarcopenia [28].

**Table 1 Tab1:** Summary of eligibility, inclusion, non-inclusion and exclusion criteria

Eligibility criteria	Inclusion criteria	Exclusion criteria
Difficulty lifting packages over 4.5 Kg	Age > 70	Patient refusal to participate to the study
Difficulty rising from low seats without help of arms	SPPB <10	Functional or locomotor disabilities
Difficulty climbing less than 10 steps of stairs	≥ 2 eligibility criteria	Life expectancy less than 6 months
Difficulty moving or reduced walking speed		A chronic disease affecting participation to the program
Difficulty walking over 400 m without break		MMSE< 20
Walking time less than 1 hour per week		
Feeling of exhaustion during domestic activity		
> 2 falls during the last year		
Involuntary weight loss (> 5% in 1 month or > 10% in 6 months)		

In the presence of 2 or more inclusion criteria, GPs will assess the patient using the Short Physical Performance Battery (SPPB) [29]. In the event of a SPPB score < 10 (out of 12), patients will be given 9 questionnaires grouped in a unique folder: Activity Scale for the Elderly (PASE) [30], weekly sedentary time inspired by Gardiner [31], Activity of daily living scale (ADL), Instrumental activities of daily living scale (IADL) [32], SF-12 scale [33], Mini-Nutritional Assessment (MNA) [34], EPICES score *(Evaluation de la précarité et des inégalités de santé dans les centres de santé (in French))* [35, 36], Charlson index [37], Geriatric Depression Scale (GDS) [38] (Table 2) that measure their autonomy, nutrition and physical activity, and will be proposed another medical appointment for inclusion in the study. If a patient refuses to participate in the study, this will be noted in the CRF.

**Table 2 Tab2:** List of questionnaires

List of questionnaires	
Physical activity	Activity Scale for the Elderly (PASE) [30]
	Weekly sedentary time inspired by Gardiner [31]
Autonomy	Activity of Daily Living scale (ADL)

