### Discussion of the study design

The study will be randomized and multicenter, and will investigate the effect of a specific clinical pathway with both the effects of the intervention and, simultaneously, the implementation of the program in current practice conditions, across various areas of France. Rather than an individual randomization, a cluster design was chosen in order to limit the risk of contamination, but also for reasons of feasibility and ethics; it would have been difficult to justify why two different patients in the same practice would not have access to the same management. Likewise, we chose to stratify randomization to ensure that GPs working in the same practice would be randomized to the same group. The high number of clusters (60 in total) and low number of patients within each cluster should help reduce the risk of bias due to intra-cluster correlation.

Despite the cluster design, the effects of the intervention will be determined individually. An open-label design is necessary given the nature of the intervention. The effects of the intervention will be evaluated using an objective outcome, the SPPB, which has shown to be reproducible [29, 39]. An SPPB score below 10 is predictive of all-cause mortality [42] and reveals a weakness of lower extremity function and higher mobility disabilities [43]. Clinically, an improvement of one point in the SPPB score is associated with substantial and clinically relevant changes in physical performance [44]. SPPB is a reliable tool to screen for patients likely to benefit from a physical exercise program [41] and it is generally considered as a valid predictive tool to assess physical performance and predict risk of mobility loss [11, 39, 42]. The GPs will screen systematically each consecutive patient over 70 years of age to limit selection bias. Furthermore, they will note each refusal to participate in order to evaluate the acceptability of the program from the patients’ perspective.

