Standard training will be provided to the participating GPs for the recruitment and to physical trainer to ensure harmonized delivery of information. All GPs will be given specific training in group sessions for the loss of mobility screening assessment, prior to randomization. This will ensure that the screening and inclusion procedure is the same for all patients, and ensure comparability between groups for the measurement of the primary outcome. Moreover, GPs in the intervention group will not be involved directly in the intervention itself.

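### The primary SPPB change is scored by an unmasked GP from the randomised practice, and the safeguards the article states do not protect it from scoring that differs by arm

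*Protocol article*

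**What the plan says.** **Endpoint and rater.** The Primary outcome section under Outcomes and measurements states: "The primary outcome will be the difference in SPPB scores between inclusion and 6-month visits". It adds: "To allow comparison, the SPPB will be evaluated by the same GP as far as possible". The Study design section gives the GP the assessments in both arms: "In both groups, GPs will perform a consultation for inclusion at baseline and two evaluations at 6 and 12 months thereafter". Under Participants, the GP also scores the SPPB that qualifies a patient for entry.

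**Knowledge of arm.** The Abstract says that "the unit of randomization will be the GP practice". The Discussion of the study design accepts that the trial has to be open label. No masked or independent assessor is described.

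**Month 3, intervention arm only.** The section on the multimodal intervention sends these patients to the GP, "who will perform an intermediate SPPB assessment in order to adapt the intensity of the intervention". A gain of less than one point leads to a repeat of the programme. Table 3 shows no month-3 SPPB for controls.

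**Safeguards offered.** The Discussion of the study design names three:
- the nature of the endpoint: "The effects of the intervention will be evaluated using an objective outcome, the SPPB, which has shown to be reproducible";
- group training of all GPs in the assessment before randomisation, meant to keep the primary measurement comparable between groups;
- the GP's distance from treatment: "Moreover, GPs in the intervention group will not be involved directly in the intervention itself".

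**The concern.** By the article's own description, the SPPB requires someone to judge three standing positions, time a short walk and time five chair rises. The result depends on instructions, encouragement, use of the stopwatch and judgement of whether a stance was held. A rater who knows the arm can shift these without intending to.

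Reproducibility concerns random error between repeated measurements. It says nothing about an error whose mean differs between arms. Keeping the same GP reduces noise between raters, but it also means that the rater is likely to know the baseline score. In the intervention arm that rater has also seen month 3, and that month-3 score has helped steer the programme.

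At stake is the single primary comparison. A lean that follows the arm adds directly to the estimated effect.

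**Working it through.** **1. Whether the planned analysis removes a lean.** Let δ be the true difference in 6-month change. Let λ_I and λ_C be the mean scoring shifts between baseline and month 6 in the intervention and control arms. The estimated treatment-by-period effect then has expectation

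δ + (λ_I − λ_C).

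Leniency that a GP applies equally at both visits cancels in the change. A shift at month 6 that differs by arm does not. The random GP effect models variation among GPs around their arm mean, so it cannot separate an arm-wide shift from δ. Intent-to-treat concerns who is analysed, not how they are measured.

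**2. Reproducing the plan's sample size.** Inputs from Sample size calculation: δ = 0.8 (1.2 against 2.0), SD 1.7, ICC ρ = 0.15, m = 5 patients per GP, k = 28 GPs per arm, power 80%. Alpha is not given there. I assume 5% two-sided, in line with the planned 95% confidence intervals.

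- Design effect: 1 + (5 − 1) × 0.15 = 1.6.
- Taking 1.7 as the SD between patients within a GP, total variance = 1.7² / (1 − 0.15) = 2.89 / 0.85 = 3.40.
- k = 2 × 3.40 × (1.96 + 0.84)² × 1.6 / (5 × 0.8²) = 26.7. With t quantiles on 2(k − 1) degrees of freedom it is 27.7, so 28. Power at 28 is 80.5%.

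The stated figure is reproduced. Taking 1.7 as the total SD gives 22.7 (normal) or 23.7 (t), which does not match 28.

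**3. Standard error of the arm difference.** SE = √(2 × 3.40 × 1.6 / (5k)):

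- k = 28: √(10.88 / 140) = 0.279. Differences above about 0.56 are significant.
- k = 30: √(10.88 / 150) = 0.269. Differences above about 0.54 are significant.

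**4. Illustrative effect of a lean.** Let b = λ_I − λ_C and δ = 0. One way to reach b = 0.2 is for one patient in five in one arm to score one point higher (1/5 × 1). Two in five gives 0.4. These values are assumptions. They are 0.2/0.8 = 25% and 0.4/0.8 = 50% of the target.

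Two-sided rejection = P(T > t_c) + P(T < −t_c), where T is noncentral t with 2(k − 1) degrees of freedom and noncentrality b/SE.

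| Assumed lean b | k = 28 | k = 30 |
|---|---|---|
| 0 | 5% | 5% |
| 0.2 | 10.9% | 11.3% |
| 0.4 | 29.1% | 30.9% |

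A normal approximation agrees. Taking SE = 0.8/(1.96 + 0.84) = 0.286 gives 10.8% and 28.8%. With 1.7 as the total SD, the ranges over k = 28 to 30 are 11.9–12.4% and 33.3–35.4%.

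**5. The GP's role, side by side.** The multimodal intervention section has the intervention GP take a month-3 measurement that, through a stated rule, decides whether the programme is repeated. The Discussion offers the GP's lack of direct involvement as support for comparable measurement. The word directly lets both sentences stand if it means delivery of the sessions. The sentence still does not show that the rater is detached from the treatment being graded.

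**The case against.** The best defence has five parts.

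- **Training.** All GPs are trained in the assessment before randomisation, expressly so that the primary measurement is comparable. This stands as a reason to expect a smaller lean. It does not mask anyone at month 6.
- **Same rater.** The preference applies to both arms, and stable leniency cancels in a change score. This also stands, but it does not reach a lean that appears only once the arm is known. The preference holds only as far as possible, so not every patient will have one rater throughout.
- **The GP statement.** A reader might infer that the article flatly contradicts itself on the GP's role. It does not: it denies direct involvement, and delivery belongs to the geriatrician, dietician and trainer. The passages need reconciling; the sentence need not be deleted as false.
- **Size and direction.** No document supports a lean of 0.2 or 0.4. That one patient in five gains a whole point is also assumed, since the article gives only a 12-point total and three dimensions. If the lean varied among GPs, the between-cluster variance would rise and the SE would not stay at 0.27–0.28. A generous month-3 score would also withhold the repeat programme, which could work against the intervention arm.
- **Unseen documents.** The full protocol or CRF may already hold raw times and a fixed script. The article's silence on these is not a defect. The point rests on what the article states: who scores, and why that is said to be safe.

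**Conclusion.** The point holds as a weakness in how the primary endpoint is assessed and defended. That the scoring GP knows the arm is inferred from the open-label design and practice-level randomisation; nothing in the article points the other way. The stated safeguards address random error, technique and delivery of treatment. None addresses a lean that follows the arm, and no planned model removes one.

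The 11% and 29% figures show sensitivity under assumed leans, no true effect, 5% two-sided alpha and an unchanged SE. They do not estimate this trial's error rate. The sample size is not in question here.

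A reader might go further and infer that a positive result could never be told apart from assessor expectation. The documents do not support that. The size of any lean is unknown, training may limit it, and hospitalisation, institutionalisation and weight depend less on the GP's timing and judgement.

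**What to change.** 1. Unless the CRF already does so, record the raw stance, walk and chair-rise times at every SPPB. Derive the score for the primary analysis centrally, without arm information. This removes lean only at conversion to points. Timing, encouragement and judgement of stances stay with the GP.
2. Complete the month-6 and month-12 SPPB forms without sight of earlier scores, using a fixed instruction script. The GP may still remember earlier results. Month 3 is left out because its rule compares with baseline.
3. In Discussion of the study design, state that the assessor is unblinded and that steps 1 and 2 reduce the bias but do not remove it. Reconcile the sentence on intervention GPs with their month-3 role in the multimodal intervention section. How the month-3 score is used is not at issue here.

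The cost is a few more CRF fields per SPPB, a paragraph in the existing GP training and a less favourable description of the endpoint. No visits or staff are added and the sample size is unchanged. An assessor masked to allocation would do more, but would need staff.

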#### Secondary outcomes

The change of the secondary outcomes between the inclusion, 6, and 12-month follow-up will be analyzed. Secondary outcomes are: physical performance evaluated by the PASE [30] and sedentary behavior inspired by Gardiner et al. [31], and the distance walking; autonomy evaluated by the ADL and IADL [32]; quality of life evaluated by the SF-12 scale [33]; the number of serious injuries, hospitalizations, and institutionalizations, falls with healthcare consumption; nutritional status: weight, BMI, albuminemia (adjusted on CRP level) and MNA [34].

Additional outcomes will estimate prevalence of patients over 70 years of age with mobility limitation, adherence of patient and GPs to the program, and describe geriatric diagnosis after the consultation for the intervention group.

At baseline, GPs will collect data from the patients social environment EPICES score) comorbidities (Charlson index) [37], depression symptoms (GDS) [38], and medication inventory.

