### Secondary outcomes

The analysis used for the primary outcome will be used to evaluate the change of the secondary outcomes between the inclusion and the 6-month follow-up visit.

The analysis of the change of secondary outcomes in the interventional group will be performed using a longitudinal mixed effect linear model with a fixed period effect and as random effects: the center, the GP, and the patient nested within the GP. This analysis will be adjusted on the age at inclusion.

A univariate analysis will be performed using a longitudinal mixed effect linear model to identify the factors associated with the SPPB result at 6 months in the interventional group. The model will include as random effects the center, the GP and the patient nested within the GP, and as fixed effect the corresponding factor. This analysis will provide the effect estimation of each factor with its 95% confidence intervals. The independent factors found significant in this univariate analysis will be included in a multivariate analysis.

All analysis will be performed using the statistical analysis program SAS® version 9.4 (SAS Institute Inc., Cary, NC, USA), and the R program, version 3.3.1 (R foundation, Vienna, Austria).

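### Change in MNA is a declared secondary outcome but MNA is scheduled at baseline only, and the article shows no follow-up or control-arm measurement for albuminemia

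*Protocol article*

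**What the plan says.** In the protocol article, the Secondary outcomes section under Outcomes and measurements states: "The change of the secondary outcomes between the inclusion, 6, and 12-month follow-up will be analyzed". The list that follows ends with "nutritional status: weight, BMI, albuminemia (adjusted on CRP level) and MNA". Under Statistical analyses, the Secondary outcomes section adds: "The analysis used for the primary outcome will be used to evaluate the change of the secondary outcomes between the inclusion and the 6-month follow-up". It also plans a longitudinal analysis of change within the intervention group, with a period effect. The aim at the end of the Background includes nutritional status among the things to be evaluated between the control and intervention groups.

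On measurement, three places matter.

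- Table 3, titled "Schedule of outcome assessments", has an MNA row with a single mark, under Baseline. The month-3, month-6 and month-12 cells are empty. The weight and BMI row is full: "Weight, BMI X X X X X X". There is no row for albumin or CRP.
- Study design describes one blood test: "In the intervention group, an initial blood test will be performed (blood cell count, CRP, pre-albuminemia, and albuminemia").
- Multimodal and multidisciplinary intervention has a second MNA, at the hospital: "a dietician from the study center will evaluate the nutritional status of patients (Mini Nutritional Assessment, weight, Body Mass Index, weight loss"). Study design places the hospital contacts at "two visits to the allocated study hospital outpatient clinic (within 2 weeks and at 3 months from inclusion"), in the intervention group.

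**The concern.** A change outcome needs a value at inclusion and at least one later value in the same patient. A between-arm comparison of change needs this in both arms. The text treats MNA as a repeated outcome, while the schedule treats it as a one-time descriptor, alongside the social score, the Charlson index and the medication inventory. Both cannot be right. For albuminemia, nothing in the article shows the measurements that the outcome requires, and the CRP adjustment rests on the same single test.

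The intervention includes an individual dietary assessment and an agreed dietary strategy, so the nutritional outcomes are where its dietary part would be expected to show. If the schedule is followed as printed, the follow-up MNA values will not be collected, and they cannot be recovered once the visits have passed.

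**Working it through.** No figure in the plan bears on this point. The check is a count of scheduled measurements against what the stated analysis needs.

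**What the analysis estimates.** The primary model, applied to the secondary outcomes, has fixed effects for intervention, period (inclusion as reference) and their interaction. For the 6-month change, apart from covariate adjustment, the interaction is

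(mean at M6 − mean at inclusion, intervention) − (mean at M6 − mean at inclusion, control).

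It needs four arm-by-time cells. The 12-month change needs the same, with M12 in place of M6.

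**Cells shown in the article.** Table 3 has one Baseline column serving both arms. Weight and BMI share a row.

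| Measure | Inclusion, interv. | Inclusion, control | M6, interv. | M6, control | M12, interv. | M12, control |
|---|---|---|---|---|---|---|
| Weight, BMI | yes | yes | yes | yes | yes | yes |
| MNA | yes | yes | empty | empty | empty | empty |
| Albumin, CRP | yes (initial test) | not shown | not shown | not shown | not shown | not shown |

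- Weight and BMI: 4 of 4 cells for the 6-month interaction.
- MNA: 2 of 4, both at inclusion. Neither the period effect nor the interaction can be estimated. A baseline comparison of arms is possible.
- Albumin and CRP: 1 of 4 shown.

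**Can other text fill the MNA cells?** The dietician's MNA is taken in the intervention arm only. The hospital contacts fall within 2 weeks and at 3 months. The intervention section makes the repeat consultation with the dietician depend on the month-3 SPPB result, whereas Study design lists the 3-month hospital visit without that condition. Under either reading there is no value at 6 or 12 months and no control counterpart, so the dietician's MNA supports neither the between-arm comparison nor a change to 6 or 12 months within the intervention arm.

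**Is the MNA row simply misread?** This is unlikely. Neighbouring rows keep their follow-up marks, so the table does distinguish repeated from one-time measures. The outcomes text also names its baseline-only items in a separate paragraph (EPICES, Charlson, GDS, medication) and does not put MNA there.

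**Result.** Two of the four listed nutritional measures (weight, BMI, albuminemia, MNA) lack the scheduled data that the stated analysis requires. For MNA this follows from a row that is present and marked at baseline only. For albuminemia it follows from the absence of any description.

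**The case against.** The strongest objection concerns albumin. The article condenses a full protocol that is not shown, and a laboratory schedule is a detail that an article may leave there. Study design calls the blood test initial; it does not say that no later test is done or that controls have none. The absence of a row in Table 3 is weak evidence, because the table is visibly imperfect: SPPB appears twice, and the footnote defines CRP and GDS although neither has a row, while GDS is collected at baseline according to the text. This objection stands. A reader might infer that no control-arm albumin value exists at any time, or that albumin is certainly taken only once. The documents do not support either statement; they support only that no follow-up or control-arm measurement is shown.

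A reader might also infer that MNA cannot be compared between arms at all. That is too strong, since it is taken at baseline in both arms. Only the change is unsupported.

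It can also be said that one planned analysis is confined to the intervention group and needs no control data. That is true, but it still needs follow-up values, and none is scheduled for MNA at 6 or 12 months. The possible incompleteness of Table 3 does not explain the MNA conflict either, because that row is present.

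**Conclusion.** The MNA part is an internal contradiction and can be stated with high confidence: change to 6 and 12 months is a declared outcome, the schedule has no MNA after baseline in either arm, and the dietician's assessment does not fill the gap. The albumin part carries less certainty: as published, the outcome has one time point in one arm, and whether more exists depends on the full protocol.

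The reach is limited to two of the four nutritional measures. As shown, only weight and BMI allow a between-arm comparison of nutritional change. The SPPB primary outcome, its model and the sample size are not affected. The conclusion assumes that Table 3 is printed as intended for the rows it contains. The documents do not show whether the outcome list or the schedule is the part in error, so the request is to reconcile them.

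**What to change.** Reconcile four places in the protocol article with each other and with the full protocol: the blood-test sentence in Study design, Table 3, the secondary outcome list, and the secondary analysis section.

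- **MNA.** Either add it at the existing month-6 and month-12 GP visits in both arms, or remove it from the change outcomes and label it a baseline descriptor. Adding it costs one short questionnaire at two visits; with the planned 300 patients that is at most 300 × 2 = 600 extra administrations, and no new visit. It is already in the baseline questionnaire folder. Relabelling costs an edit and the loss of that outcome.
- **Albumin and CRP.** If the full protocol has follow-up and control-arm measurements, show them in Table 3 and correct the blood-test sentence. If it does not, remove albuminemia as a change outcome and label it a baseline descriptor of the intervention arm.
- **Statement of outcomes.** If both measures are withdrawn, name weight and BMI as the nutritional outcomes that can be compared between arms.

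The trial is registered and has ethics approval, so withdrawing or relabelling a stated outcome should go through a dated, documented amendment that is disclosed when results are reported. That administrative step is the main cost of the deletion route.
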